#### Cost-effectiveness analysis

It is assumed that the point estimates for differences in mean cost and QALY between the intervention and control groups will be 1000 SEK and 0.18 QALY, respectively, with differences in the SDs for cost and QALY of 5000 SEK and 0.26 QALY, respectively. The sample size of 260 (130 per group) provides 0.84 power, assuming that the WTP is 1.3 million SEK [64,65].

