## Methods/design

### Study design

The study is a 6-month randomized controlled lifestyle behavior intervention trial, where intervention and control groups are followed at 3 and 6 months. Written informed consent will be obtained before randomization. Eligible participants not willing to participate will be registered as such.

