### Economic evaluation

Cost-effectiveness analysis will be performed from patient, health care and societal perspectives. In the societal perspective, all costs are included irrespective of who is burdened by them, while the health care perspective is only concerned with costs burdening the health care sector. The patient perspective focuses on the costs that the patients have to bear to change their lifestyle habits through the intervention. The societal perspective is generally preferred, although a health care perspective supplies additional (affordability) information and can strengthen conclusions based on the societal perspective. The results will be presented in terms of incremental cost-effectiveness ratios (ICERs), which show the change in costs for an incremental benefit [19]. To determine the cost-effectiveness of the intervention, ICERs will be calculated for all statistically significant outcomes. In cost utility analysis, utility values will be calculated using the EQ-5D questionnaire which provides the health related quality of life as quality adjusted life years (QALY).

We will perform economic evaluation in two different time horizons; short-term (within-trial) and long-term. Within-trial economic evaluation will only focus on the trial cost data and the outcomes. For long-term duration, we will develop a decision analytic model based on the outcome of the trail. This will be done by extrapolating the secondary clinical outcomes (BMI, blood pressure, lipid profile) to predict future disease events such as CVD, diabetes and diabetes-related complications. Each disease event will have a future cost and QALY. Future costs and effects will be discounted by 3% per year, but we intend to perform sensitivity analyses on other rates [58]. We will analyze uncertainty by both one-way and multi-way sensitivity analysis, and also by non-parametric bootstrapping. We will calculate 95% confidence intervals for the ICERs.

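### The stated 0.84 power for the cost-effectiveness analysis does not follow from its own inputs, which give about 0.9998, and the assumed 0.18 QALY gain has no stated time horizon

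*Protocol article*

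**What the plan says.** The protocol article's sample-size section has a subsection on the cost-effectiveness analysis. The assumed effects are "differences in mean cost and QALY between the intervention and control groups will be 1000 SEK and 0.18 QALY, respectively". Variability comes next, in loose wording: "with differences in the SDs for cost and QALY of 5000 SEK and 0.26 QALY, respectively". The subsection then concludes: "The sample size of 260 (130 per group) provides 0.84 power, assuming that the WTP is 1.3 million SEK". No alpha, no correlation between cost and effect, and no period for the 0.18 QALY are given.

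Two other sections bear on the horizon. Study design says: "The study is a 6-month randomized controlled lifestyle behavior intervention trial". Economic evaluation plans two horizons. For the short one, "Within-trial economic evaluation will only focus on the trial cost data and the outcomes". For the long one, a decision model will extrapolate trial results on BMI, blood pressure and lipids to later disease events. EQ-5D, the source of the QALYs, is collected at baseline, 3 and 6 months.

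**The concern.** The subsection prints nearly everything needed to compute the power, so a reader can check it, and the check fails by a wide margin. A standardised QALY difference of 0.18/0.26 = 0.69 is large, and 130 per group detects a difference of that size almost with certainty. A power of 0.84 looks far too low for these inputs.

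The 0.18 QALY looks too high for the follow-up. Half a year of full health is only 0.5 QALY, so 0.18 would be more than a third of everything a participant could accrue in the trial.

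The two problems pull in opposite directions: the stated power is too low for the stated inputs, while the stated gain, if it is a 6-month gain, is too high to expect. Cost-effectiveness is the last of the four stated aims, and this subsection tells the reader that it is adequately powered. As written, that assurance cannot be relied on.

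**Working it through.** **Inputs** (protocol article, Cost-effectiveness analysis): cost difference ΔC = 1000 SEK; QALY difference ΔQ = 0.18; SDs 5000 SEK and 0.26 QALY; willingness to pay λ = 1,300,000 SEK per QALY; n = 130 per group, already net of dropout.

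**Assumptions where the protocol is silent:** the SDs are per-arm SDs; alpha is 0.05 two-sided; the correlation ρ runs over its whole range.

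**1. Attempt to reproduce 0.84**

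- Incremental net benefit = λΔQ − ΔC = 1,300,000 × 0.18 − 1000 = 233,000 SEK.
- SD of net benefit = √[(λ·SD_Q)² + SD_C² − 2ρ·λ·SD_Q·SD_C], with λ·SD_Q = 338,000 and SD_C = 5000. This gives 338,037 SEK at ρ = 0, 333,000 at ρ = +1 and 343,000 at ρ = −1.
- Standard error of the difference = SD × √(2/130) = 41,928 SEK at ρ = 0.
- z = 233,000 / 41,928 = 5.56 (5.48 to 5.64 over all ρ).
- Power = Φ(5.56 − 1.96) = 0.9998 (0.99978 to 0.99988 over all ρ).

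Correlation is immaterial because 338,000 dwarfs 5000.

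**2. Other readings tried**

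| Reading | Power |
|---|---|
| Two-sided alpha 0.01 | 0.998–0.999 |
| Two-sided alpha 0.001 (ρ = 0) | 0.988 |
| QALY difference alone | 0.9999 |
| Cost difference alone | 0.36 |
| 65 per group (ρ = 0) | 0.976 |
| SD multiplied by √2 (ρ = 0) | 0.976 |
| SD doubled (ρ = 0) | 0.79 |

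None returns 0.84.

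**3. What 0.84 would correspond to** (ρ = 0, two-sided 0.05; z-values 1.960 + 0.994 = 2.954)

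- Stated effect and SDs: n = 2 × 2.954² × (338,037/233,000)² = 36.7, so 37 per group.
- 130 per group and the stated SDs: detectable net benefit = 2.954 × 41,928 ≈ 123,900 SEK, so ΔQ = (123,900 + 1000)/1,300,000 ≈ 0.096 QALY.
- 130 per group and the stated effect: a QALY SD of about 0.49 instead of 0.26.
- All else as stated: a willingness to pay of roughly 20,000 SEK at ρ = 0 (power 0.83), against the stated 1.3 million.

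**4. What 0.18 QALY means if it is a 6-month gain**

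- Gap present from day one and held for 0.5 year: 0.18/0.5 = 0.36 utility.
- Equal baselines and the same gap u at 3 and 6 months, by the trapezoidal rule: gain = 0.125u + 0.25u = 0.375u, so u = 0.18/0.375 = 0.48.
- Equal baselines and a linear rise to 6 months: 0.18/0.25 = 0.72 at month 6.
- With utility capped at 1, instant full health for every intervention participant reaches 0.18 only if control utility averages 1 − 0.36 = 0.64 or less.

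**5. Illustration only.** The utility gains and the smaller SDs here are assumptions, not protocol figures. Gains of 0.03 to 0.05 at 3 and 6 months are 0.011 to 0.019 QALY. At 130 per group and ρ = 0, two-sided power is 6–9% with QALY SD 0.26, and 10–30% with SD 0.10–0.13.

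**The case against.** The inputs are not fully defined. The wording on the SDs is loose, no alpha is given, and the references cited for the calculation might use a different method. This has some force: the SD reading matters numerically, since doubling the SD brings power down to 0.79, so 0.9998 must be quoted with its reading and alpha. It does not rescue 0.84, which no reading tried returns. Taken literally, a difference between SDs leaves the SDs themselves undefined, and then no power can be derived at all.

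A reader might infer that the 0.18 QALY is simply unattainable in this trial. The document does not support that without a condition. It never says that 0.18 is a 6-month gain, and it plans a long-term model as well. Nor can the long-term reading be dismissed because a modelled gain has no sampling error: the model is to be built on participants' outcomes, and bootstrapping and confidence intervals for the cost-effectiveness ratios are planned, so its precision can depend on the number of participants. What stands is narrower. A plain comparison of two group means is not the calculation for such a modelled quantity. The protocol also gives no baseline EQ-5D value, so calling the 6-month reading implausible is a judgement, resting on the required utility gaps of 0.36 to 0.72.

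A reader might also infer that true within-trial power is a small fraction of 0.84 and that an inconclusive result is likely. That depends on utility gains and SDs that the document does not contain.

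Finally, the primary outcome is fasting glucose, which has its own power statement, and the expected 260 completers are derived from eligibility, participation and dropout. The cost-effectiveness figure does not set the trial's size. This stands in full and limits the seriousness of the point.

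**Conclusion.** The stated power is wrong for its stated inputs: about 0.9998 against 0.84, given a net-benefit comparison, per-arm SDs and two-sided alpha 0.05, for any correlation. At two-sided alpha 0.01 it is still 0.998 to 0.999. Where the 0.84 came from cannot be established from the document.

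The missing horizon is a second, conditional defect. If 0.18 QALY is a within-trial gain, it is implausible over 6 months. If it is a long-term modelled gain, the calculation shown does not fit it. In neither case does the subsection support a claim of adequate power for the economic aim. How much power the trial really has for that aim cannot be determined from the document. This is a correction to a secondary aim: randomisation, enrolment and the primary analysis are untouched.

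**What to change.** Withdraw the 0.84. Do not just substitute a figure above 0.999: that would repair the arithmetic and leave a claim resting on an unexplained gain.

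State over what period the 0.18 QALY accrues and what the 5000 SEK and 0.26 QALY are (per-arm SDs or something else). Then do one of two things:

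- restate power for within-trial net benefit using 6-month inputs: expected cost difference and QALY gain, per-arm SDs, correlation, willingness to pay, and alpha with its sidedness; or
- declare the economic evaluation estimation-based, with intervals and no power claim.

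If 0.18 belongs to the long-term model, say so and take it out of the sample-size section.

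The cost is a rewritten paragraph and probably a less favourable claim. The number recruited and the primary-outcome calculation do not change.

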### Univariate and multivariate analysis

The trial data will be analyzed on an intention-to-treat basis. Bivariate and multivariate analyses will assess the effects of the intervention (compared to controls) on fasting glucose level, weight, physical activity level and dietary intakes, with adjustment for age and gender, and will identify factors that can predict beneficial and non-beneficial responses to the intervention (*e.g.* baseline physical activity, motivation, attitude, adherence to the intervention). Continuous data will be analyzed with paired Student’s t-tests and linear regression, and categorical variables with chi square tests and logistic regression with 95% confidence intervals.

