**Methods/design:**

In this randomized controlled trial, 308 participants (born in Iraq, living in Malmö, Sweden and at high risk of type 2 diabetes) will be allocated to either a culturally adapted intervention or a control group. The intervention will consist of 10 group counseling sessions focusing on diet, physical activity and behavioral change over 6 months, and the offer of exercise sessions. Cultural adaptation includes gender-specific exercise sessions, and counseling by a health coach community member. The control group will receive the information about healthy lifestyle habits provided by the primary health care center. The primary outcome is change in fasting glucose level. Secondary outcomes are changes in body mass index, insulin sensitivity, physical activity, food habits and health-related quality of life. Measurements will be taken at baseline, after 3 and 6 months. Data will be analyzed by the intention-to-treat approach. The cost-effectiveness during the trial period and over the longer term will be assessed by simulation modeling from patient, health care and societal perspectives.

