#### Randomization/blinding

Subjects agreeing to participate will be randomly allocated to the intervention (n = 155) or control group (n = 155). Randomization will be stratified by age, gender, prediabetes and FINDRISC score, with the aim of obtaining an equal distribution of participants between the two groups. Spouses will be randomized to the same group, and spouses not fulfilling the inclusion criteria will be invited to participate in the study by supporting their husband or wife.

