## Statistical analysis

### Sample size and power calculation

#### Fasting glucose

From the baseline study and earlier intervention studies on Arabic participants, we estimate a standard deviation (SD) of fasting glucose of 0.6 [12,63]. Based on earlier studies, we assume that the true difference between the intervention and control group means is 0.22 mmol/L [12,63]. We will be able to reject the null hypothesis that the population means of the intervention and control groups are equal with a power of 0.86.

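### The stated adjustment for age and gender omits baseline fasting glucose and two of the four randomization factors, which costs precision but does not bias the estimate

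*Protocol article*

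**What the plan says.** The section on univariate and multivariate analysis describes bivariate and multivariate analyses of the intervention effect on fasting glucose, weight, physical activity and dietary intake, "with adjustment for age and gender, and will identify factors" that predict a good or poor response. Continuous data are to be analyzed by paired t-tests and linear regression.

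The section on randomization and blinding states: "Randomization will be stratified by age, gender, prediabetes and FINDRISC score". Two of these four factors, age and gender, reappear in the analysis. The other two do not.

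The abstract states: "The primary outcome is change in fasting glucose level". It also states: "Measurements will be taken at baseline, after 3 and 6 months". Table 1 lists fasting plasma glucose at screening, baseline, 3 months and 6 months.

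The power section for fasting glucose says "we estimate a standard deviation (SD) of fasting glucose of 0.6", assumes that "the true difference between the intervention and control group means is 0.22 mmol/L", and concludes that the trial can "reject the null hypothesis that the population means of the intervention and control groups are equal" with a power of 0.86.

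No section adds baseline fasting glucose, prediabetes or FINDRISC to the model for the intervention effect. The other variables named (baseline physical activity, motivation, attitude, adherence, insulin sensitivity, disposition index, family history) are predictors or modifiers of response, not adjustment covariates for the comparison between arms.

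**The concern.** The baseline value of a continuous outcome is usually its strongest available predictor. Here it is measured in every participant and then left out of the stated covariates. If the analysis uses the 6-month level, the baseline value is not used at all. If it uses change, baseline enters only by subtraction. Subtraction gives baseline a fixed coefficient of one, where a fitted coefficient would leave less residual variance.

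Prediabetes and FINDRISC were thought important enough to balance by design. When a prognostic factor is balanced by stratification and then left out of the model, its variance stays in the residual, and the standard error is larger than the design warrants.

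At stake is the precision of the main comparison in a trial planned with little power to spare.

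**Working it through.** **Inputs from the article.** SD 0.6, difference 0.22 mmol/L, stated power 0.86, 130 completers per arm (260 of 310 after about 16% drop-out).

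**Assumptions not in the article.** Two-sided alpha 0.05. Equal SDs at baseline and follow-up. Baseline-to-follow-up correlation r, shown over a range. The covariate gain from age and gender cannot be derived from the article, so the unadjusted figures stand in for the stated model.

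**Formula.** Power = Φ(0.22 / (SD × √(2/130)) − 1.96).

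**Step 1: the stated power.** The standard error is 0.6 × √(2/130) = 0.0744. Then 0.22/0.0744 = 2.956, and Φ(2.956 − 1.96) = Φ(0.996) = 0.84. This is close to the stated 0.86, just below it. A power of 0.86 would take 138 per arm.

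**Step 2: residual SD under each analysis.** The article does not settle whether 0.6 is the SD of the level or of the change, so both readings are shown.

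- 0.6 as SD of the level: follow-up level, 0.6; change score, 0.6 × √(2(1 − r)); baseline-adjusted, 0.6 × √(1 − r²).
- 0.6 as SD of change: change score, 0.6; baseline-adjusted, 0.6 × √((1 + r)/2).

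**Step 3: power at 130 per arm, with the residual SD in brackets.**

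| Reading of 0.6 | Analysis | r = 0.4 | r = 0.5 | r = 0.6 |
|---|---|---|---|---|
| SD of level | Follow-up level, unadjusted | 0.84 (0.600) | 0.84 (0.600) | 0.84 (0.600) |
| SD of level | Change, unadjusted | 0.77 (0.657) | 0.84 (0.600) | 0.91 (0.537) |
| SD of level | Baseline-adjusted | 0.90 (0.550) | 0.93 (0.520) | 0.96 (0.480) |
| SD of change | Change, unadjusted | 0.84 (0.600) | 0.84 (0.600) | 0.84 (0.600) |
| SD of change | Baseline-adjusted | 0.94 (0.502) | 0.93 (0.520) | 0.91 (0.537) |

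Over the wider range r = 0.3 to 0.8, adjusted power is 0.873 to 0.998 if 0.6 is the SD of the level, and 0.956 down to 0.876 if it is the SD of change. Both stay above 0.86 throughout.

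**Step 4: variance saved against a change score.** The ratio of adjusted to change-score variance is (1 − r²) / (2(1 − r)) = (1 + r)/2. It is 0.65 at r = 0.3 and 0.85 at r = 0.7, a reduction of 35% and 15%. The ratio is below 1 for every r below 1, and 1 − r² is below 1 for every r other than 0. So for 0 < r < 1, adjustment gains over both unadjusted analyses.

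**Step 5: where a change score falls below 0.86, if 0.6 is the SD of the level.** Power 0.86 needs 0.22/SE = 1.96 + 1.08 = 3.04, so SE = 0.0724 and SD = 0.0724/√(2/130) = 0.583. Setting 0.6 × √(2(1 − r)) = 0.583 gives r of about 0.53. Below that, a change-score analysis has less than the stated power.

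**Step 6: the strata.** The article gives nothing from which to compute the extra gain from prediabetes and FINDRISC. Prediabetes is defined partly by fasting glucose, so it may add little once baseline glucose is in the model.

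**The case against.** The strongest case against the point is that this is a condensed article and the analysis sentence is a summary. It covers four outcomes at once, labels no model as primary, does not give the dependent variable, and does not call its covariate list complete. A reader might infer that the plan commits to a primary regression with age and gender only. The text does not say that. What stands is that a covariate set is named for the effect on fasting glucose and does not match the randomization. That is a stated choice, not a silence.

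Other stronger readings also go too far:

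- **That 0.6 is definitely the SD of the level, so the power calculation used the wrong quantity.** The wording leans that way, but it cites earlier studies and does not settle the matter. If 0.6 is the SD of change, unadjusted change-score power is 0.84 whatever r is, and no shortfall arises at low correlation.
- **That the trial is underpowered.** On the SD-of-level reading this depends on r. At r = 0.6 a change score reaches 0.91, above plan. The stated power claims no covariate gain, so forgoing one does not undermine it.
- **That the estimate is biased or exposed to serious baseline imbalance.** Under randomization, omitting these covariates causes no bias on average. Stratifying by prediabetes, itself defined by glucose cut-offs, limits chance imbalance in baseline glucose without removing it.

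The equal-SD assumption also deserves caution: excluding people with diabetes truncates glucose at entry but not at follow-up. This affects the exact figures. With unequal SDs, a fitted baseline coefficient still leaves no more residual variance than a coefficient fixed at zero or one.

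**Conclusion.** The point holds as a matter of efficiency. The stated adjustment omits the baseline value of the primary outcome and half of the stratification factors, although all of them are already available. For r from 0.4 to 0.6, baseline adjustment raises power from between 0.77 and 0.91 to between 0.90 and 0.96, depending on the analysis and on the reading of the SD. At r = 0.5 both readings give 0.93, and 104 per arm would reach the stated 0.86 instead of 138.

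The sizes rest on an assumed r, an assumed two-sided 5% level and equal SDs. The direction does not depend on r. The added value of the two missing strata cannot be quantified from the article. Including them makes the analysis follow the design and avoids standard errors that are too large. Validity is not in question.

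**What to change.** Amend the analysis section so that 6-month fasting glucose, or its change, is regressed on arm, baseline fasting glucose, age, gender, prediabetes status and FINDRISC score, with the adjusted difference between arms reported as the main estimate. With baseline in the model, the level and the change give the same estimated arm difference, so either may be the dependent variable. For the other continuous outcomes listed there, use each outcome's own baseline value plus the same four stratification factors. A mixed model that also uses the 3-month measurement is optional and not needed to correct this point.

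The cost is a change of wording, made before unblinded data are seen. No further data, visits or participants are required.

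### The only t-test named for continuous outcomes is paired, which examines change within an arm; the plan does not say that the between-arm regression decides

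*Protocol article*

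**What the plan says.** The section on univariate and multivariate analysis gives the purpose as a comparison of arms: "Bivariate and multivariate analyses will assess the effects of the intervention (compared to controls) on fasting glucose level, weight, physical activity level and dietary intakes". Age and gender are the planned adjustment variables. The section then names the methods: "Continuous data will be analyzed with paired Student’s t-tests and linear regression, and categorical variables with chi square tests". Logistic regression is added for the categorical variables. No independent-samples t-test appears anywhere in the article.

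The sample size section for fasting glucose is framed as a two-group comparison. It assumes that "the true difference between the intervention and control group means is 0.22 mmol/L", with "we estimate a standard deviation (SD) of fasting glucose of 0.6", and says the trial can "reject the null hypothesis that the population means of the intervention and control groups are equal with a power of 0.86". The abstract gives change in fasting glucose as the primary outcome.

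Under randomization, 155 participants are allocated to each arm. Spouses go to the same arm, and nothing matches an intervention participant to a control. Under the control group heading, nurses advise controls to be more active, to lose weight and to change their diet in the same way as the intervention group.

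**The concern.** With unmatched parallel arms, the only pairs available for a paired t-test of glucose are two measurements on the same person. That test asks whether one arm changed over time. It does not ask whether the arms differ, which is both the stated purpose of the analysis and the hypothesis that was powered.

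The difference matters because both arms may move together. Controls receive lifestyle advice, and everyone is measured at baseline, 3 and 6 months. A significant fall within the intervention arm could then reflect a change shared with controls. Finding significance in one arm and not in the other is not a test of the difference between them. The article names a paired test and a regression side by side without saying which one carries the conclusion, so a within-arm p-value on the primary outcome stays available as evidence of effect.

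**Working it through.** **1. Which hypothesis was powered?** Inputs from the article: difference 0.22 mmol/L, SD 0.6 (unit taken as mmol/L), 130 completers per arm. Two-sided alpha of 0.05 is assumed, because the article does not state it.

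- Two independent groups: SE = 0.6 × √(2/130) = 0.0744; 0.22/0.0744 = 2.956; power = Φ(2.956 − 1.960) = 0.84. The article states 0.86, so this is close.
- One paired sample of 130 with the SD of change set at 0.6: SE = 0.6/√130 = 0.0526; 0.22/0.0526 = 4.181; power = Φ(4.181 − 1.960) = 0.987. This is not close.

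The stated power therefore belongs to a two-group comparison, as its wording says.

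**2. What can a paired test show when there is no intervention effect?** Simulation with 130 per arm, SD of change assumed 0.6, 20,000 runs, the same true change in both arms, all tests two-sided at 5%:

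| Shared change (mmol/L) | Paired test significant in intervention arm | Significant in intervention, not in control | Between-arm two-sample test significant |
|---|---|---|---|
| 0 | 5.1% | 4.8% | 4.9% |
| −0.05 | 16% | 13% | 4.7% |
| −0.10 | 47% | 25% | 4.8% |
| −0.15 | 81% | 15% | 4.9% |

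The between-arm test holds its 5% level whatever the shared change. The paired test does not, because it is testing something else.

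**3. How far does the figure depend on assumptions?** The article gives neither the correlation r between baseline and follow-up glucose nor an expected shared fall c, so both are assumed and ranged.

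- SD of change = 0.6 × √(2(1 − r)).
- Chance p of a significant fall within one arm = Φ(c/(SD of change/√130) − 1.96).
- Chance of a significant fall in the intervention arm and not in the control arm = p(1 − p).

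At r = 0.6 and c = 0.10: SD of change = 0.537; SE = 0.0471; p = Φ(2.125 − 1.96) = 0.565; p(1 − p) = 0.246.

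| r | c = 0.10 | c = 0.15 |
|---|---|---|
| 0.3 | 23% | 22% |
| 0.6 | 25% | 10% |
| 0.8 | 13% | 0.5% |

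The quantity p(1 − p) cannot exceed 25%. It becomes small when the shared fall is large relative to its standard error, because both arms are then significant. At r = 0.6 it is 15% for a fall of 0.05. With no shared fall it is 2.4%, the ordinary one-direction error; the simulation's 4.8% counts both directions.

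**4. Does the correction disturb the sample size?** With a true difference of 0.22 and SD of change 0.6, the independent two-sample comparison had power 0.839 in simulation, against 0.84 by formula. The power basis needs no change on this account.

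**The case against.** The strongest reply is that a valid between-arm method is already in the same sentence. The effect is to be adjusted for age and gender, which a t-test cannot do, so the adjusted effect has to come from linear regression. With arm as a predictor, that regression estimates the difference between arms and matches the powered hypothesis. This stands. A reader might infer that the plan has no valid between-arm method; the document does not support that.

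Three other stronger readings also go beyond the text.

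- **That the paired t-test is the primary analysis.** Nothing labels it so. Reading it as the bivariate test and regression as the multivariate one is an inference from the parallel with chi square and logistic regression. The paired tests may be meant only to describe change within arms.
- **That both arms must fall through regression to the mean.** The eligibility section admits people on FINDRISC alone, and its IGT category requires fasting glucose below 6.1 mmol/L. The assessment schedule has a trial baseline separate from screening, with fasting glucose at both, so much of any regression from the selecting measurement may already have happened. A shared change remains plausible because of the control-arm advice, without this mechanism.
- **That 25% is the trial's false-positive rate.** It applies only under a rule of significance in one arm alone, which the article never states, and under assumed values of r and c.

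What survives is narrower. A paired test is named in a paragraph whose purpose is comparison with controls, and the text does not say that the regression decides. This is not detail left to an unseen analysis plan, because the type of test is written down.

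**Conclusion.** The point holds in limited form. The paired t-test, the only t-test named, cannot serve the stated purpose or test the powered hypothesis. The regression named beside it can, provided arm is a predictor, but it is not identified as the test of effect. The mismatch follows from the design and needs no numerical assumption.

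The size of the harm is conditional. If an effect were claimed from significance in the intervention arm only, the chance of a false claim would be about 25% for a shared fall of 0.10 mmol/L at r = 0.6. It would be about 0.5% to 25% over r = 0.3 to 0.8 and falls of 0.10 to 0.15 mmol/L. If the regression on arm decides, the error stays near 5%. The point bears on the primary outcome and should be settled before the data are analysed.

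**What to change.** In the section on univariate and multivariate analysis:

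- State that the test of effect is the between-arm difference in fasting glucose at 6 months, with its 95% confidence interval, from linear regression with arm, baseline fasting glucose, and the age and gender adjustment already planned.
- Replace the paired t-test with an independent-samples comparison of change as the unadjusted version.
- Keep within-arm changes as description only, not as evidence of an intervention effect.

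The cost is a sentence or two of rewording. It needs no new data and no change to the sample size.
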